**Fig. 9 Fig9:**
[figure not shown]
Virtual 1st-person view from VRCE or PCE in the craving induction task

**Table 4 Tab4:** Schedule for the PICOC study

		**Study period**			
	**Enrolment and allocation**	**Post-allocation**			**1-month follow-up**
**TIMEPOINT**	**T0**	**T1**		**T2**	**T3**
	**Week 0**	**Week 1**	**Week 2**	**Week 3**	**Week 7**
**ENROLMENT:**					
**Eligibility screen**	X				
**Informed consent**	X				
**Allocation**	X				
**INTERVENTIONS:**					
**Experimental group**					
**VRCET MFCT**		--------------------------			
				-----------	
**Active control group**					
**PCET**		--------------------------			
**ASSESSMENTS:**					
**CEQ-F, TLFB, DERS, AWARE, QCBDU ** ^**a**^	X		X	X	X
**In cue exposure (CET only):** **CEQ-S, orally assessed cocaine craving, SPIE ** ^**b**^ **, ITC-SOPI ** ^**c**^		X	X	X	
**In VRE to cocaine cues:** **CEQ-S, BMIS, DTCQ-8D, blood pulse, skin temperature and conductance**	X		X	X	X
**Cocaine urine test strip**	X		X	X	X
**CSQ-8**			X	X	

^a^ For each new exposure situation encountered; ^b^ ITC-SOPI Ecological validity subscale; ^c^ QCBDU – Beliefs Related to Addiction subscale

Secondary outcomes will consist of:Assessing the effects after 2 weeks of treatment (V1; VRCET vs. PCET), post-treatment (V2; VRCET + vs. PCET), and 1-month post-treatment (V3; VRCET + vs. PCET) on cocaine use-related measures (abstinence, risk of relapse, emotional dysregulation, and dysfunctional thoughts) measured via urinary samples and self-reported questionnaires.Negative cocaine urine test strips will be used for objectively support participant self-reports of cocaine abstinence [55].Timeline Followback (TLFB) mean total scores will be used for subjectively assess participants cocaine abstinence in within the last 21 days, ranging from 0 (“none”) to 100 (“total abstinence”; [56]).Advance Warning of Relapse (AWARE) mean total scores will be used to subjectively assess the decrease of participants risk of cocaine use relapse within the next 2 months, ranging from 25 (11 to 37%-risk) to 193 (53 to + 95%-risk; [57]).The Difficulties in Emotion Regulation Scale (DERS) mean total scores will be used to subjectively assess the decrease of participant emotional dysregulation, ranging from 36 (“Almost never”) to 180 (“Almost always”; [58]).The Questionnaire of Core Beliefs related to Drug Use and Craving (QCBDU) – Beliefs Related to Addiction mean total scores will be used to subjectively assess the decrease of participant identification to dysfunctional thoughts related to CUD, ranging from 0 (“Strongly disagree”) to 72 (“Strongly agree”; [59]).Assessing at V0 the effects of VRCE to cocaine cues on cue-specific cocaine craving-related subjective (cocaine craving, emotional states, self-efficacy to cope with craving), physiological reactivity (blood pulse, skin temperature and conductance), and cue-exposure specific measures (sense of presence and ecological validity), as compared with PCE. The physiological measures and the self-reported measures will be administered, respectively, during and immediately after a 7-min VRE or PCE to a cocaine-related situation, with similar scenario to the CET situation 5 (Table 1), but with different virtual environments, avatar, and item appearances (Fig. 9).
The dispersion of blood pulse, skin temperature, and conductance signals will be used through PLUX Biosignals physiological captors (medical device certification: ISO 13485) to assess the cue-specific reactivity in VRCE compared to PCE.The CEQ-S mean total scores will be used to subjectively assess cocaine craving intensity in participants exposed to VRCE compared to PCE; items range from 11 (“not at all”) to 110 (“extremely”; [54]).The Brief Mood Introspection Scale (BMIS) mean total scores will be used to subjectively assess negative and positive emotional states in participants exposed to VRCE compared to PCE. Items range from 0 (“definitely do not feel”) to 21 (“definitely feel”; negative emotions) or 27 (positive emotions; [60]).The Drug Taking Confidence Questionnaire – 8 (DTCQ-8) mean total scores will be used to subjectively assess the self-efficacy to cope with cocaine craving in participants exposed to VRCE compared with PCE; items range from 0 (“not at all confident”) to 800 (“very confident”; [61]).The Spatial Presence for Immersive Environments (SPIE) – Spatial Presence subscale mean total scores will be used to subjectively assess the sense of presence experienced by participants exposed to VRCE compared with PCE; items range from 4 (“strongly disagree”) to 20 (“strongly agree”; [62].The Spatial Presence for Immersive Environments (SPIE) – Realism subscale mean total scores will be used to subjectively assess the increased sense of reality experienced by participants exposed to VRCE compared with PCE, ranging from 4 (“strongly disagree”) to 15 (“strongly agree”; [62]).The Independent Television Commission Sense of Presence Inventory (ITC-SOPI) – Ecological Validity subscale mean total scores will be used to subjectively assess the increased sense of ecological validity experienced by participants exposed to VRCE compared to PCE; items range from 5 (“strongly disagree”) to 25 (“strongly agree”; [25]).Assessing the cognitive, behavioral, or emotional factors (cocaine craving, dysfunctional thoughts, cocaine use, and emotional dysregulation) mediating the efficacy of VRCET+ in decreasing self-reported cocaine craving. The CEQ – F, QCBDU, TLFB, and DERS mean total scores will be used to subjectively assess, as aforementioned, cocaine craving frequency (last 14 days), dysfunctional thoughts regarding CUD, cocaine abstinence (last 21 days), and difficulties in emotion regulation.Assessing the acceptability of (i) our intensive VRCET as a stand-alone (after 2 weeks of treatment; V1) or add-on (post-treatment; V2; VRCET +) intervention and (ii) VRE as a cue-exposure paradigm, for each new VRE performed in therapy.The Spatial Presence for Immersive Environments (SPIE) – Cybersickness subscale mean total scores will be used to subjectively assess acceptable cybersickness symptoms (i.e., < 7) experienced by participants exposed to VRCE; items range from 0 (“strongly disagree”) to 10 (“strongly agree”; [62]).The Client Satisfaction Questionnaire – 8 (CSQ-8) mean total scores will be used to subjectively assess satisfaction levels towards psychotherapeutic services (≥ 21; “good”); items range from 8 to 32 [63].

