#### In and post-treatment measuring times (V1, V2, and V3)

The first measuring time (T1) will take place after 2 weeks of treatment, at the 11th treatment session and prior to start the MFCT (experimental arm) or second PCET (active control arm) phase. This will thus allow for comparing short-term research primary and secondary outcomes between VRCET and PCET, after 10 consecutive sessions of exposure.

The second measurement time (T2) will take place at the end of treatment (week 3), at the 15th and last treatment session. This will thus allow for comparing short-term research primary and secondary outcomes between VRCET + (10-session VRCET and 5-session MFCT) and PCET, after 15 consecutive sessions.

The third and last measuring time (T3) will consist in a follow-up visit taking place 1 month after the end of treatment (week 8). This will thus allow for comparing medium-term research primary and secondary outcomes between VRCET + (10-session VRCET and 5-session MFCT) and PCET, 1 month after 15 consecutive sessions of each therapeutic arm. Patients’ participation will end after this visit.

For each of these measurement times, subjective self-report questionnaires and objectives measures related to research objectives will be administered (Fig. 10).

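### The fixed 21-day TLFB window nearly fits T2, but it puts 6 to 7 pre-treatment days into the T1 abstinence score and leaves the first one to two weeks after treatment outside the T3 score

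*Protocol article*

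**What the plan says.** Outcomes {12} describes the TLFB score as a subjective measure of "participants cocaine abstinence in within the last 21 days", on a scale from 0 to 100 where 100 is total abstinence. The paragraph on mediating factors in the same section repeats the window: "cocaine abstinence (last 21 days". No window specific to a visit, or running from the previous visit, is given.

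The TLFB belongs to the cocaine-use measures whose aim is "Assessing the effects after 2 weeks of treatment (V1; VRCET vs. PCET), post-treatment (V2; VRCET + vs. PCET), and 1-month post-treatment (V3; VRCET + vs. PCET"). The Table 4 row "CEQ-F, TLFB, DERS, AWARE, QCBDU" is marked at T0, T1, T2 and T3.

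The visit times are in Participant timeline {13}:
- **T1:** "The first measuring time (T1) will take place after 2 weeks of treatment", and more exactly "at the 11th treatment session and prior to start the MFCT".
- **T2:** "at the 15th and last treatment session".
- **T3:** "1 month after the end of treatment (week 8"). Table 4 heads the T3 column week 7.

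Sessions run daily from Monday to Friday, and therapy starts within one week of the inclusion visit.

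**The concern.** The visits are not equally spaced, but the look-back is the same length at each. A 21-day window matches the three-week treatment course. It is longer than the treatment received by T1 and shorter than the interval between the end of treatment and T3.

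At T1 the score mixes days under treatment with days that treatment could not affect. T1 matters because it is the only visit that compares VRCET with PCET before MFCT is added to the experimental arm. The other dated self-report, CEQ-F, looks back 14 days, which does match the time under treatment at T1.

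At T3 the score is silent on the days just after treatment ends. The Background raises a possible increase in relapse risk after cue exposure and gives relapse prevention as a reason for adding MFCT, so those days bear on the trial's own question. The T3 urine strip is scheduled only at that visit, so nothing in Table 4 is planned to cover the gap.

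**Working it through.** **Inputs.** Window: 21 days (Outcomes {12}). Sessions: Monday to Friday for three weeks; T1 at session 11 and T2 at session 15 (Participant timeline {13}). T3: week 8 (same section) or week 7 (Table 4).

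**Calendar.** Let day 1 be the Monday of week 1. Session k falls on day 7 × floor((k − 1)/5) + ((k − 1) mod 5) + 1.
- Session 11: 7 × 2 + 0 + 1 = day 15.
- Session 15: 7 × 2 + 4 + 1 = day 19.

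The protocol does not say whether the visit day counts, so both conventions are shown. The window ends either the day before the visit (A) or on the visit day (B), and starts 20 days before it ends. Pre-treatment days are those numbered 0 or lower.

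| Visit | Day | Window A | Pre-treatment, A | Window B | Pre-treatment, B |
|---|---|---|---|---|---|
| T1 | 15 | −6 to 14 | 7 of 21 (33%) | −5 to 15 | 6 of 21 (29%) |
| T2 | 19 | −2 to 18 | 3 of 21 (14%) | −1 to 19 | 2 of 21 (10%) |

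**Effect at T1.** Let p0 be the share of abstinent days before treatment, equal in the two arms, and let pE and pC be the shares during treatment. Under A, each arm's score is 100 × (7 × p0 + 14 × p)/21. The between-arm difference is therefore 100 × (14/21) × (pE − pC), or 0.67 of the difference over the treatment days. Under B the factor is 15/21 = 0.71.

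**Coverage at T3.** Treatment ends on day 19. Assume that T3 falls on the same weekday as T2. Uncovered days run from day 20 to the day before the T3 window opens.

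| T3 placed at | Day | Uncovered, A | Uncovered, B |
|---|---|---|---|
| Week 7 (19 + 28) | 47 | days 20–25: 6 of 27 (22%) | days 20–26: 7 of 28 (25%) |
| Week 8 (19 + 35) | 54 | days 20–32: 13 of 34 (38%) | days 20–33: 14 of 35 (40%) |

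If one month is instead read as 30 or 31 days, 8 to 10 days are uncovered. The T2 window ends on day 18 or 19, so it does not reach these days either.

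**The case against.** The strongest case for the plan is that 21 days equals the treatment length and almost fits T2, the end point of the T0-to-T2 change that Statistical methods {20a} names as the primary inference. An equal look-back at baseline and later visits also keeps change scores on a common footing. That stands, and it is why 21 days should stay at T0 and T2. It does not answer T1 or T3, which the protocol also names as abstinence comparisons.

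A second objection is that a journal article leaves visit-specific scoring to the full protocol or the analysis plan. The point does not rest on missing detail, though. The article states one window, states it twice, and schedules the instrument at four visits.

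A reader might also infer more than the documents support:
- **That the T1 comparison is biased.** The pre-treatment days enter both randomised arms alike. They dilute the difference and do not favour an arm.
- **That a third of the power is lost.** The factor of 0.67 applies to the raw mean difference. Power depends on the standardised difference, and the document gives no variances for the TLFB.
- **That the mediation analysis is diluted.** Outcomes {12} lists the TLFB among the mediators but does not say at which visit.
- **That T3 is mis-scored.** A participant who used in the first week and then abstained for 21 days is scored correctly under the stated definition. The limit is one of coverage.
- **That the overlap of the T1 and T2 windows is itself a fault.** They share 17 of 21 days, but any scoring from treatment start would also nest one inside the other.

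The upper T3 figures depend on the separate week 7 and week 8 discrepancy, so they are a range and not an estimate.

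**Conclusion.** The point holds as a mismatch between a stated window and two of the stated visits, for one secondary self-reported outcome. At T1 about a third of the scored days precede treatment, and the raw between-arm difference falls to roughly two thirds. This assumes that the arms are alike on those days and that the difference in daily abstinence applies across all treatment days. At T3, between about a fifth and two fifths of the post-treatment interval goes unobserved by the TLFB, depending on which T3 week applies and whether the visit day counts. Read as abstinence over the follow-up month, the T3 score would claim more than it measures. The primary craving outcome is not affected. The change is worth making, but the conduct of the trial does not hinge on it.

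**What to change.** - **T1:** for the between-arm comparison, score the percentage of abstinent days from treatment start to T1 (14 days). The 0 to 100 scale is unchanged.
- **T0 and T2:** keep 21 days.
- **T3:** extend the calendar back to the last session and report the percentage of abstinent days since the end of treatment. Keep the 21-day score as a supplement, for continuity with participants already assessed. Where the extension is not possible, label the result as the last 21 days and not as abstinence over the follow-up month.
- **T3 timing:** reconcile week 7 in Table 4 with week 8 in Participant timeline {13}, so that the length of the follow-up interval is fixed.

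The cost is small but real. T3 needs one to two more weeks of recall. Look-back lengths will differ between visits, so trends across visits must be read with that in mind. T1 can be re-scored only if day-level TLFB entries are kept, whereas the article mentions only total scores. Recruitment began in May 2023, so some participants may have only the 21-day T3 score.

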### Objectives {7}

The primary objective of our parallel randomized controlled trial is to evaluate the efficacy and acceptability of an intensive 3-week VRCET-based psychotherapy (VRCET +), i.e., VRCET + MFCT, in reducing self-reported cocaine craving in inpatients hospitalized for CUD, by comparing its immediate post-treatment effects to the ones of a traditional PCET.

The secondary objectives of our trial will be:To evaluate the effects after 2 weeks of treatment (V1; VRCET vs. CET), post-treatment (V2; VRCET + vs. PCET), and 1-month post-treatment (V3; VRCET + vs. PCET) on urinary, physiological, and self-reported measures of cocaine use-related measures (abstinence, risk of relapse, self-efficacy to cope with craving, emotional dysregulation, and identification to dysfunctional thoughts)To evaluate the effects of VRE to cocaine cues on cue-specific cocaine craving-related measures (cocaine craving, emotional states, self-efficacy to cope with craving) and cue-exposure specific measures (sense of presence, ecological validity, cybersickness) compared to a traditional non-VR pictures-based cue-exposure (PCE).To evaluate the cognitive, behavioral, or emotional factors (cocaine craving, self-efficacy to cope with craving, dysfunctional thoughts, cocaine use and emotional dysregulation) mediating the efficacy of VRCET + in decreasing self-reported cocaine craving.To evaluate the acceptability of (i) our intensive VRCET as a stand-alone (V1) or add-on (V2; VRCET +) therapeutic intervention via client satisfaction towards psychotherapeutic services measures and (ii) VRE, as a cue-exposure paradigm via cybersickness self-reported measures.

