##### Experimental arm (VRCET +)

The experimental arm (VRCET +) will consist in an intensive 3-week treatment of 10 meetings of VRCET, followed by 5 meetings of MFCT. All meetings will last 90 min and will be delivered on 5 consecutive days, i.e., Monday to Friday. VRCET meetings will take place in a 2 consecutive weeks period (weeks 1 and 2). MFCT meetings will take place in the 1-week period following VRCET (week 3).

##### Virtual reality cue-exposure therapy (VRCET)—weeks 1 and 2

VRCET will be performed using Meta Quest 2 VR headset. The VR application used in the present trial was designed by the ICube and LPC laboratories (Strasbourg University) in collaboration with the Saint-Esprit and Martinique Hospital Centers. The exposure setting is interactive, visually, and audio immersive (360° and first-person view). Participants will be able to virtually rotate and move their head, hands, and their upper body thanks to a 6 degrees of freedom headset/hand controllers’ system. Participants will remain seated on a 360°-rotating stool and will be able to move around in VR environments thanks to a laser-guided teleportation (Figs. 1 and 2). Finally, participants will see and use virtual hands to grasp, hold, and move virtual trivial or cocaine-related objects, as outlined in Table 1.

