#### Randomization

Eligible patients will be randomized by the research psychiatrist or psychologist in charge of the inclusion visit, using the Research Electronic Data Capture (REDCap) secure web application, in the VRCET + (experimental) or PCET (active control) therapeutic arm.

After randomization, participants will be invited to complete baseline self-reported measures as well as to perform a craving induction task related to primary and secondary research objectives. This craving induction task will consist of three 7-min 30 exposures and will systematically start with one VRE to neutral cues, followed by one VRE and one PCE to a cocaine-related situation. The order of these two exposures to cocaine cues (i.e., VRE thus PCE or PCE thus VRE) will be randomly counterbalanced for controlling for potential cue-induced carry-over effect between one exposure to the other. The exposures’ order sequence generation for each participant will be generated by the research methodologist, using the Research Randomizer secure web application, and provided to the investigator within sealed opaque envelope for the inclusion visit.

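### With a neutral run in VR only, the V0 task cannot separate cue-specific physiological reactivity in VR versus pictures from the effect of the medium itself

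*Protocol article*

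**What the plan says.** Participant timeline {13}, under Randomization, describes the V0 craving induction task. It "will systematically start with one VRE to neutral cues, followed by one VRE and one PCE to a cocaine-related situation". Of the three runs, only the two with cocaine content change places between patients: "The order of these two exposures to cocaine cues (i.e., VRE thus PCE or PCE thus VRE) will be randomly counterbalanced". The neutral VR run is always first, and no neutral picture run is described.

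Outcomes {12} names the physiological endpoint: "The dispersion of blood pulse, skin temperature, and conductance signals will be used". Its stated purpose is "to assess the cue-specific reactivity in VRCE compared to PCE". The timing, for physiology and then for self-reports, is "during and immediately after a 7-min VRE or PCE to a cocaine-related situation". The text does not say whether they are also taken in the neutral run, or how that run enters the analysis.

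The same label appears more loosely in two other places. Objectives {7} has "To evaluate the effects of VRE to cocaine cues on cue-specific cocaine craving-related measures", and the heading sentence of this outcome group in Outcomes {12} has "Assessing at V0 the effects of VRCE to cocaine cues on cue-specific cocaine craving-related subjective". There it covers craving, emotional states and self-efficacy. The individual sentences for CEQ-S, BMIS and DTCQ-8 speak only of scores in patients exposed to VRCE compared with PCE.

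**The concern.** A difference between media in cue-specific reactivity is a medium-by-cue interaction: the response to cocaine cues over neutral content in VR, compared with the same quantity in pictures. The task supplies the neutral reference for one medium only.

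The media differ in more than their cocaine content. The intervention description says of VR that "Participants will be able to virtually rotate and move their head, hands, and their upper body", while the picture exposure is seated, on a laptop and non-interactive. These descriptions are of the therapy sessions, but the V0 runs use the same two media. The dispersion of pulse, temperature and conductance signals can respond to movement and general arousal with no cocaine cue present. A physiological VR-picture difference could then be reported as stronger cocaine-cue reactivity when it came wholly from the medium. A medium effect of opposite sign could equally hide a real VR advantage.

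**Working it through.** **Reproducing the plan's figure.** There is none on this point. Sample size {14} concerns the between-arm comparison only, and no effect size or power is given for the V0 contrast.

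**Inputs from the protocol article.** Three runs per patient and their order (Participant timeline {13}). 54 randomised patients, threshold 0.05, two-tailed (Sample size {14}; the last two are stated for the between-arm test and borrowed here).

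**Inputs assumed.** Medium effect m = 0.2, 0.3 or 0.5 SD; within-patient correlation r = 0.5 (range 0.3 to 0.7); equal variances; a paired t-test.

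**Step 1: what the runs identify.** Let a be the patient's level, v the medium effect of VR relative to pictures, and c_v and c_p the responses to cocaine cues in VR and in pictures.

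- neutral VR = a + v
- cocaine VR = a + v + c_v
- cocaine pictures = a + c_p

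Cocaine VR − cocaine pictures = v + (c_v − c_p).

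Referencing both cocaine runs to neutral VR: (cocaine VR − neutral VR) − (cocaine pictures − neutral VR) = cocaine VR − cocaine pictures. The neutral run cancels, so the result is again v + (c_v − c_p). In simulation the two versions gave the same p-values to about 1e-15.

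Cocaine VR − neutral VR = c_v, apart from order. Nothing in the three runs separates c_p from v. Counterbalancing the two cocaine runs addresses carry-over between them and leaves v in place. This step needs no assumed number.

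**Step 2: illustration of size.** Set c_v = c_p, so there is no cue-specific difference. The standardised paired effect is dz = m / √(2(1 − r)). At r = 0.5 the divisor is 1 and dz = m. The noncentrality is dz·√54, for example 0.5 × 7.348 = 3.67. Chance of a significant result (two-sided 0.05, n = 54):

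| m (SD) | r = 0.3 | r = 0.5 | r = 0.7 |
|---|---|---|---|
| 0.2 | 23% | 30% | 46% |
| 0.3 | 45% | 58% | 80% |
| 0.5 | 86% | 95% | 99.6% |

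With 43 patients (an assumed 20% loss: 54 × 0.8 = 43.2) and r = 0.5, the figures are 25%, 48% and 89%. At alpha 0.05/3 (assuming a Bonferroni correction over three pairwise contrasts), n = 54 and r = 0.5, they are 17%, 40% and 88%.

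**Step 3: a design with a neutral run in each medium.** The contrast (cocaine VR − neutral VR) − (cocaine pictures − neutral pictures) removes v. In 20,000 simulated trials per setting it rejected in 4.7% to 5.3% for every medium effect from 0 to 0.8 SD, at n = 54 and n = 43. With equal variances its SD is √2 times larger, so a true dz of 0.5 becomes 0.5/1.414 = 0.35, and power at n = 54 falls from 95% to about 72%.

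**The case against.** The strongest reply concerns scope, and much of it stands.

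- In Objectives {7} and the heading sentence in Outcomes {12}, cue-specific can be read as the name of a group of measures, set beside the measures specific to the exposure medium. No interaction hypothesis is written there. The CEQ-S, BMIS and DTCQ-8 sentences already describe a total VR-picture contrast. Only the physiology sentence plainly claims cue-specific reactivity between media.
- The Discussion expects VR to induce more craving because it is immersive, interactive and three-dimensional. The medium is then part of the question. A reader might infer that the whole V0 comparison, or the Discussion's claim about craving, is invalid. The document does not support that.
- Handling virtual cocaine is itself cue content, so interaction in VR is not all nuisance.
- Novelty is reduced by a tutorial VR task at inclusion and by the neutral VR run placed first, and patients with cybersickness symptoms are excluded. This makes a large novelty effect less plausible but does not remove a medium effect.
- The rejection rates are a power curve for assumed medium effects. A reader might take 30% to 95% as the trial's type I error. It is not: the documents give no medium effect, and for the total VR-picture difference a rejection would be correct. The paired t-test is also assumed; the only within-patient tests that Statistical methods {20a} names are Friedman, Wilcoxon signed-rank and Sign tests, as fallbacks for non-normal data.

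What does not stand is the reply that an analysis plan could settle the matter. How the neutral run is used is analysis detail. That c_p and v are inseparable follows from the runs themselves.

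**Conclusion.** The point holds in a limited form. The three V0 runs cannot identify a cue-specific VR-versus-picture difference, although Outcomes {12} assigns that meaning to the physiological signals. It also touches BMIS if the label in Objectives {7} and Outcomes {12} is taken literally, because mood can shift with the medium alone. CEQ-S and DTCQ-8 remain interpretable as total VR-picture differences. Presence, realism and ecological validity are unaffected, since there the medium difference is the target. The randomised primary comparison is unaffected.

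The identification result rests only on the stated runs. Its practical size depends on a medium effect of unknown size and sign; under the assumptions shown, 0.2 to 0.5 SD would yield significance in about 30% to 95% of trials with no cue-specific difference. This is a secondary baseline outcome and the repair is cheap, but it changes what may be concluded from a positive physiological result.

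**What to change.** 1. In Outcomes {12}, rename the physiological VR-picture contrast as the total response to VR versus picture exposure (medium plus cues).
2. In Objectives {7} and the heading sentence in Outcomes {12}, either drop cue-specific for the VR-picture comparison or state that it only names a group of measures.
3. State that a physiological or mood difference between VR and pictures will not be interpreted as stronger cocaine-cue reactivity in VR.
4. Report cocaine VR minus neutral VR as within-VR cue reactivity, confirming that the measures are taken in the neutral run. Add the caveat that neutral VR always comes first, so this contrast is mixed with order and habituation.

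These changes affect wording and analysis only; the cost is a narrower secondary claim.

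A neutral picture run is needed only if the sponsor wants to keep the cue-specific VR-versus-picture claim. It would add about 7 minutes at V0, its place in the sequence would have to be fixed, and it could apply only to patients still to be enrolled (Trial status gives recruitment as open from May 2023). It would also give the noisier contrast shown in the working, at about 72% instead of 95% power for dz 0.5 with all 54 patients, and less with only the remaining ones.
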